### Blinding and strategies to deal with expectation and motivation effects

Outcome assessors will be blinded to group allocation of participants. To prevent disclosure of group assignment by participants, we will remind them at the last telephone interview (t_5_) not to bring the solved jigsaw puzzles to the posttest assessment. Second, we will remind them at the last telephone interview (t_5_) and immediately before the posttest assessment (t_6_) not to tell the assessor anything that may give hints to the allocated group. Here, the participants will also sign a confirmation statement that they received this information. Blinding participants to the assigned group is by nature not feasible. Given the lack of a double-blind design, several strategies will serve to reduce potentially different expectations and motivation between groups [49]. First, implementing an additional component in both groups (i.e., cognitive health counseling) aims to induce similar positive expectations regarding cognitive benefits (cf. component control design; [49, 50]). Second, the investigators will tell all participants before disclosure of group assignment that (a) both groups should benefit cognitively from the cognitive health counseling and that (b) it is currently not known whether solving jigsaw puzzles has a positive impact on cognition. Third, participants of both groups will receive the same amount of study staff contact during the intervention period (apart from questions regarding jigsaw puzzle experiences and adherence) and the same opportunities to express their concerns and to receive attention (face-to-face health counseling, three telephone calls, and the possibility to contact the study staff whenever wished). As differential expectations between groups are still likely to some degree and cannot be completely excluded, the study assesses expectations on a continuous and on a categorical scale in the last telephone call approximately 9 days before the follow-up test (see confounding variables section). We avoid an assessment at the follow-up, as this might either influence test performance through activated expectations (when assessed directly before the neuropsychological tests) or might alter expectations according to test performance (when assessed directly after the neuropsychological tests) [49]. In addition, we will aim to keep test motivation high in both groups by asking participants again, directly before the follow up, whether they want to receive their normed individual test results after study completion. One item on a 5-point rating scale at the posttest assessment (t_6_) will assess test motivation.

### Prevention of dropouts, noncompliance, and missing data

To ensure the application of the intention-to-treat principle, great effort must be invested to prevent dropouts, noncompliance, and missing outcome data, which introduce deviation from the randomization scheme [51, 52]. We will use different strategies including good personal contact through the telephone-based counseling; payment of 20€ for pretest and posttest assessments; communication of personal neuropsychological test results after the posttest assessments; interest in solving jigsaw puzzles and time commitment as study inclusion criteria; good availability of appointments for the pretest and posttest assessments (if appointments are not possible within the 2-week pretest and posttest period, we will arrange them as close as possible to this period); reminders for the posttest appointment at the last telephone-based counseling (t_5_); also if participants do not adhere to the intervention protocol, we will ask them to complete the posttest assessment; construction of a global ability score that allows some amount of missing data in the neuropsychological test battery; and prevention of excessive and insufficient mental demands through a large number of jigsaw puzzle difficulty levels (200 to 1500 piece puzzles; 2.8 × 3.0 cm to 1.8 × 1.7 cm piece sizes), adapted according to participants’ preferences, jigsaw puzzle experiences, and performance.

### Statistical analysis

The primary efficacy analysis will be based on mixed-effects models' group × time interaction [53] in an intention-to-treat approach [54] that includes all randomly assigned participants with follow-up observations. Effect sizes will include standardized differences in the pretest-posttest change scores between both groups. Standardization will be based on (1) baseline scores and (2) pretest-posttest change scores. In additional analyses, we will account for potential confounding variables such as baseline performance, the number of challenging social, physical, and cognitive activities performed in the past 4 weeks, the pretest-posttest change in these activities, Mediterranean diet in the past 4 weeks, and pre-posttest change in diet, age, education, participants’ test motivation at the posttest assessment, and their expectations of cognitive benefits.

As the primary intention-to-treat analysis is a conservative method, which may underestimate the true effect size of solving jigsaw puzzles for individuals who follow the protocol, we will use a supportive per-protocol analysis, which includes only participants who completed at least 80% of the jigsaw puzzle protocol (≥24 jigsaw puzzle days with a minimum of 45 min). With this supportive analysis, we do not only assess the robustness of effects, but may also receive a more accurate estimate of the true effect size given optimal conditions.

For subgroup and moderator analyses, pre-specified variables comprise baseline global visuospatial cognition, amount of lifetime puzzle experience, number of challenging social, physical, and cognitive activities within the intervention period, age, MMSE, and experienced pleasure in solving jigsaw puzzles.

Finally, we will assess cognitive demands of solving jigsaw puzzles and the transfer potential of gains in jigsaw puzzle skill on gains in the study outcomes by calculating the correlation between jigsaw puzzle skill in the 40-piece puzzle and the study outcomes at baseline.

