#### Primary outcome

A composite score of global visuospatial cognition will depict the primary outcome reducing α-error inflation [28]. This score will constitute the average of the eight, *z*-standardized visuospatial cognitive ability scores that include visual perception, visuoconstruction, mental rotation, processing speed, flexibility, working memory, reasoning, and episodic memory (see “Secondary outcomes”). We will calculate the individual composite scores, if at least five cognitive ability scores are available for both pretest and posttest for an individual. Analysis will be based on individuals for whom both pretest and posttest ability scores are available. We will *z*-standardize all test scores based on pretest means and standard deviations.

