### Randomization

We will use stratified, blocked randomization to avoid baseline differences in age and cognitive status between the cognitive health counseling group and the jigsaw puzzle group, while at the same time achieving groups of similar sizes. We will stratify participants into two age bands (50–64 years and 65 years and older) and two cognitive status bands (MMSE: 24–27 and 28–30) resulting in four strata (stratum 1, age ≥ 64 years, MMSE 28–30; stratum 2, age ≥ 64 years, MMSE 24–27; stratum 3, age 50–64 years, MMSE 28–30; and stratum 4, age 50–64 years, MMSE 24–27). In each stratum, randomized allocation of the participants will happen in blocks of four (two participants to each group) using the online randomization software random.org (https://www.random.org/). [name] will generate the random allocation sequence for each stratum and conceal it in sequentially numbered opaque envelopes which we will store in a separate box for each stratum. [name], PF, and DL will conduct the telephone-based pre-screening. DL, [name], or HA will enroll participants after on-site assessment of the MMSE inclusion criterion and conduct the blinded assessment. [name] or PF will conduct the face-to-face cognitive health counseling. Immediately afterwards, they will disclose group assignment. Thus, the research staff responsible for enrollment and the first part of the cognitive health counseling will be blinded to group assignment and not able to predict future group assignment.

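### The primary group × time test is valid and adequately powered, but it leaves baseline and the two stratification factors unadjusted and so gives up a small, free gain in precision

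*Protocol article*

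**What the plan says.** Protocol article, Statistical analysis: the primary efficacy test is the mixed-effects model's "group × time interaction [53] in an intention-to-treat approach [54"]. No covariates are named for this model. Effect sizes are to be standardized differences in pretest-posttest change.

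The same section then continues: "In additional analyses, we will account for potential confounding variables such as baseline performance". Age comes later in that list, next to variables measured after randomization: "pre-posttest change in diet, age, education, participants’ test motivation at the posttest assessment, and their expectations of cognitive benefits". MMSE is not in the list. It appears only among the pre-specified subgroup and moderator variables: "age, MMSE, and experienced pleasure in solving jigsaw puzzles".

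Randomization: "We will stratify participants into two age bands (50–64 years and 65 years and older) and two cognitive status bands". The stratification factors are therefore age band and MMSE band.

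Primary outcome: "Analysis will be based on individuals for whom both pretest and posttest ability scores are available". Every participant in the primary analysis thus contributes a complete pair.

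**The concern.** A mixed model with two time points, a separate baseline mean in each arm and complete pairs estimates the group × time interaction as the difference between arms in mean change. The baseline score enters as an outcome row and is subtracted with weight 1. After randomization the efficient weight is the regression slope of posttest on baseline, which equals r when the two SDs are equal. Weight 1 over-corrects by 1−r, which adds variance and passes that fraction of any chance baseline difference into the estimate.

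A mixed model that constrains the baseline means to be equal across arms would already recover this. The article does not state such a constraint, and giving baseline performance a separate role in additional analyses points against it.

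The two factors that shaped the allocation also have no stated place in the primary model. What is at stake is precision, not validity: the type I error and the average unbiasedness of the planned test are not in question.

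**Working it through.** **Inputs.** From Power analysis: 50 per group, 15% dropout (100 × 0.85 = 85 analysed), f = 0.1, r = .85, α = 0.05, stated power 90%. Assumptions made here: equal SDs at pretest and posttest, equal arms, two-sided test.

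**1. Reproduce the plan's figure.** For the within-between interaction with m = 2 occasions, λ = f²·N·m/(1−r) = 0.01 × 85 × 2/0.15 = 11.33 on 1 and 83 df. Power is 91.4% (91.1% at N = 84, 91.7% at N = 86), which agrees with the stated 90%.

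**2. Put the effect on the SD scale.** For a change-score difference δ, λ = δ²·N/[4 × 2(1−r)]. Setting this equal to 2f²N/(1−r) gives δ = 4f = 0.40 SD. The power calculation is therefore already that of the unadjusted change-score test.

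**3. Compare variances** (per participant, in units of the baseline variance).
- Change score: 2(1−r)
- Baseline-adjusted: 1−r²
- Ratio: (1−r²)/[2(1−r)] = (1+r)/2

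| r | 2(1−r) | 1−r² | Ratio | SE reduction | Power for 0.40 SD, unadjusted → adjusted | Equivalent N |
|---|---|---|---|---|---|---|
| .85 | 0.30 | 0.2775 | 0.925 | 3.8% | 91.4% → 93.3% | 85/0.925 = 91.9 |
| .80 | 0.40 | 0.36 | 0.90 | 5.1% | 82.2% → 85.9% | 85/0.90 = 94.4 |
| .70 | 0.60 | 0.51 | 0.85 | 7.8% | 65.3% → 72.3% | 85/0.85 = 100 |

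In the planning case the standard error is √(0.30 × 4/85) = 0.119 SD unadjusted and √(0.2775 × 4/85) = 0.114 SD adjusted. For 90% power at r = .85 the unadjusted test needs 81 analysed and the adjusted test 75.

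The ratio is the large-sample one. Estimating the slope costs a factor of about 1 + 1/(N−4) = 82/81, so the ratio at r = .85 is nearer 0.925 × 82/81 = 0.936 and the power about 93.0%. The conclusion does not change.

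**4. Chance baseline imbalance.** The SE of the baseline difference is √(4/85) = 0.217 SD. The change-score estimate shifts by (1−r) times the imbalance:
- one-SE imbalance: 0.15 × 0.217 = 0.033 SD at r = .85
- 1.96-SE imbalance: 0.064 SD at r = .85 and 0.085 SD at r = .80, which is 16% and 21% of the 0.40 SD planning effect

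**5. Strata.** In a simulated complete-pair data set, adding age band and MMSE band as main effects to the group × time model left the interaction at 0.4826 and its standard error at 0.11733. They can help only as band × time terms or inside a baseline-adjusted model. The article does not say how well they predict posttest given baseline. If they explained 2%, 5% or 10% of the ANCOVA residual variance (an assumed range), power at r = .85 would be 93.7%, 94.4% or 95.4%.

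**The case against.** The strongest defence is that nothing here is an error. The planned test is valid, matches the stated change-score effect size and is the test that the power calculation describes. At the protocol's own r the power target is met without adjustment and the gain is about 2 points. A one-SE baseline imbalance moves the estimate by 0.033 SD against a standard error of 0.119. Leaving out stratification factors usually makes a test mildly conservative. All of this stands and limits the point to an efficiency gain.

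It can also be said that model terms belong in a SAP that is not shown. That carries weight for the strata: their gain is unquantified, and the adjustment list is open-ended, so the absence of MMSE from it proves little. It does not carry for baseline performance, which the article itself assigns to a non-primary role.

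The case r = .80 is not the planning value. It is still worth showing: under Secondary outcomes the protocol provides for a retest reliability of the primary outcome below .80 (as a trigger for double data entry). Two of the eight components also use different figures at pretest and posttest.

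Two stronger readings are tempting. A reader might infer that the trial has little power for anything below 0.40 SD. By the same calculation at r = .85, unadjusted power is 83% at 0.35 SD and 70% at 0.30 SD. It falls to 38% only at 0.20 SD, where adjustment gives just 41%. A reader might also infer that the plan sets a less efficient primary estimate against a more efficient secondary one, with a risk of conflict. The document does not support that: the primary test is clearly named, and the additional analyses list variables measured after randomization, so they are not a clean baseline-adjusted estimate.

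**Conclusion.** The point holds as a missed improvement, not as a flaw in validity or in the power statement. With complete pairs the primary test is an unadjusted change-score comparison. Baseline adjustment would multiply its variance by (1+r)/2, worth about 7 completers at r = .85 and about 9 at r = .80, and would remove the conditional effect of chance baseline imbalance. The size rests on equal SDs at the two occasions, 85 completers split evenly, and the planning correlation, which the trial has yet to confirm; the gain grows if r is lower. For the strata, the case is agreement between design and analysis, and no gain can be claimed from this document.

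**What to change.** Define the primary model as one of two near-equivalent forms:
- ANCOVA of the posttest composite on the pretest composite and group, with age band and MMSE band as covariates; or
- a mixed model with baseline means constrained equal across arms, plus age band × time and MMSE band × time terms.

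Code the bands as they were used for allocation. The Randomization section gives the lower limit of the older band as 65 in one place and 64 in another, so this needs to be settled.

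State that variables measured after randomization (change in activities or diet, expectations, posttest motivation) stay out of the primary model. Retain the unadjusted group × time interaction as a sensitivity analysis.

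The cost is wording in the analysis plan, to be fixed before unblinded data are seen. Pretest scores, age and MMSE are all collected before allocation is disclosed, so no new data or participants are needed.

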### Procedure

The Ethics Committee of Ulm University approved this study. We will invite individuals interested in participating in the study to a telephone-based interview. Here, they will receive detailed study information and give oral informed consent. A pre-screening will assess eligibility (t_1_, see Figs. 1 and 2). At an appointment at Ulm University, successfully pre-screened participants will be able to give written informed consent and will undergo further screening (t_2A_). For included participants, the procedure will consist of a 1.5-h pretest assessment composed of neuropsychological tests and questionnaires (t_2B_) followed by the face-to-face cognitive health counseling (t_2C_). Subsequently, non-blinded study staff will disclose the group allocation to the participants (t_2D_). Within 2 weeks after the baseline assessment, the 5-week intervention period will start. We will contact all participants three times via telephone for cognitive health counseling and the assessment of adverse events (AEs, t_3_ – t_5_). These telephone-based interviews will also serve to monitor the jigsaw puzzle experience and protocol adherence in the jigsaw puzzle group. Within 2 weeks after the intervention period, we will assess the same outcomes as in the pretest assessments in the 1.5-h posttest assessment at Ulm University (t_6_). Psychologists who are blind to group allocation will conduct the pretest and posttest assessments.

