#### Power analysis

The probability to find a significant effect with 50 included participants per group, a dropout rate of 15%, a small true effect size of *f* = 0.1, pretest-posttest correlation of *r* = .85, and an α-error of 0.05 is 90%. We used G*Power 3.1.6. for power analysis [55].

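### The primary analysis is labelled intention-to-treat but is restricted to participants with both pretest and posttest, although the planned mixed model could keep every randomised participant with a pretest.

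*Protocol article*

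**What the plan says.** All places are in the protocol article.

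- **Statistical analysis.** "The primary efficacy analysis will be based on mixed-effects models' group × time interaction", in an "intention-to-treat approach [54] that includes all randomly assigned participants with follow-up observations".
- **Primary outcome.** "Analysis will be based on individuals for whom both pretest and posttest ability scores are available". The composite itself is calculated only "if at least five cognitive ability scores are available for both pretest and posttest for an individual". A randomised participant who misses the posttest therefore has no primary outcome at either visit.
- **Power analysis.** 50 participants per group, "a dropout rate of 15" per cent, f = 0.1, pretest-posttest correlation 0.85, α 0.05, stated power 90%.
- **Prevention of dropouts, noncompliance, and missing data.** To protect the intention-to-treat principle, the authors want to avoid "missing outcome data, which introduce deviation from the randomization scheme". Non-adherers are still followed: "also if participants do not adhere to the intervention protocol, we will ask them to complete the posttest assessment".
- **Procedure.** The pretest and the face-to-face counseling come first. "Subsequently, non-blinded study staff will disclose the group allocation to the participants".

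**The concern.** The label and the set do not match. The protocol treats missing outcomes as a departure from the randomisation scheme, then defines its primary set so that the people with missing outcomes are removed.

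The restriction also takes away what the chosen model could offer. A likelihood-based mixed model can use a participant who has only a pretest, and because allocation is disclosed after the pretest, every randomised participant should have one. Once the data are cut to complete pairs at two visits, the group × time test is the two-sample comparison of change scores.

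Dropout related to baseline could plausibly differ by arm. One arm is asked to puzzle for at least an hour on 30 days. The other was recruited for its interest in puzzles and asked to abstain until after the posttest. If low scorers leave one arm more readily than the other, regression to the mean among those who remain differs between arms and enters the treatment estimate.

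**Working it through.** **1. Inputs.** From Power analysis: N = 100 (50 per arm), dropout 15%, f = 0.1, ρ = 0.85, α = 0.05. Two groups and m = 2 visits. Scores are in SD units of the outcome, with equal variance at both visits. The dropout patterns in step 5 are assumptions, because the protocol gives only the overall 15%.

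**2. The protocol's own power figure.** For the repeated-measures within-between interaction, λ = f²·N·m/(1−ρ), with 1 and N−2 degrees of freedom.

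- N = 85: λ = 0.01 × 85 × 2 / 0.15 = 11.33, power 91.4%.
- N = 100: λ = 13.33, power 95.1%.

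The stated 90% is reproduced, to within 2 points, only with the dropouts removed. The power calculation therefore rests on completers too.

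**3. The planned difference.** With 42.5 per arm, λ = d²·n/(4(1−ρ)), so d = √(11.33 × 4 × 0.15 / 42.5) = 0.40 SD in change.

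**4. Precision with and without the pretest-only participants.**

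- Completers: variance = 2 × 2(1−ρ)/42.5 = 0.01412, standard error 0.119.
- All pretests kept: variance = 2 × [(1−ρ²)/42.5 + (1−ρ)²/50] = 2 × (0.00653 + 0.00045) = 0.01396.
- Ratio 0.989. Power goes from 91.4% to 91.7%.

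**5. Bias when dropout depends on the pretest.** At ρ = 0.85 the expected change falls by 1−ρ = 0.15 SD for each SD of pretest score. If completers' mean pretest is shifted by s_J in the jigsaw arm and s_C in the counseling arm, the completers' contrast is off by −0.15 × (s_J − s_C). Large-sample simulation with a logistic dropout model and true effect 0 gave:

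| Assumed dropout (jigsaw / counseling) | Shift s_J / s_C | −0.15 × difference | Completers, simulated | All pretests, simulated |
|---|---|---|---|---|
| 15% low scorers / 15% low scorers | 0.133 / 0.134 | 0.000 | −0.001 | −0.001 |
| 15% low scorers / 15% random | 0.131 / 0.000 | −0.020 | −0.021 | −0.001 |
| 15% low scorers / 15% high scorers | 0.129 / −0.133 | −0.039 | −0.040 | 0.000 |
| 25% low scorers / 5% random | 0.214 / 0.001 | −0.032 | −0.032 | +0.001 |

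Against the planned 0.40, 0.02 is 5% and 0.04 is 10%. A separate run had a true effect of 0.40, roughly 20 to 25% dropout related to low baseline in the jigsaw arm, and 10% random dropout in the counseling arm. It gave 0.369 for completers and 0.401 for the likelihood model on all pretests.

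**The case against.** Much of the case for leaving the plan alone is sound.

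- **The restriction is stated openly**, in the same sentence as the label, so nobody is misled about who is analysed. This stands; the fault is in the label and the set.
- **The set is complete-case only at visit level.** Up to three of the eight ability scores may be missing, and non-adherers who attend the posttest are kept. The protocol also lists payment, feedback of results, flexible appointments and reminders to limit dropout. This stands.
- **The bias is small** beside a standard error of about 0.12, and rests on dropout patterns that the protocol does not give. This stands and limits the weight of the point.
- **A planned analysis already handles this pattern.** The Statistical analysis section lists additional analyses that account for baseline performance. In a scenario like the last one above, completers adjusted for baseline gave 0.401. This also stands, but that analysis is additional; the primary result would still come from the unadjusted group × time contrast.

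Three stronger readings are tempting and not supported.

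- A reader might infer that the planned test needs data missing completely at random. It does not: the first row of the table shows no bias when baseline-related dropout is the same in both arms.
- A reader might infer that the restriction overstates the effect by 18 to 25%. If the 15% (or 20%) who leave the jigsaw arm gained nothing, the effect in all randomised would be 0.40 × 0.85 = 0.34 (or 0.40 × 0.80 = 0.32), and 0.40/0.34 = 1.18 (0.40/0.32 = 1.25). But that loss lies in unseen posttests. In simulation of the 15% case, completers and the model with all pretests both gave 0.401, so lifting the restriction would not cure it.
- A reader might infer that the protocol's description of intention-to-treat as conservative fails. That description is relative to participants who follow the protocol, and non-adherers with a posttest remain in the set. The table's low-scorer patterns also pull the estimate toward the null when the true effect is positive.

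**Conclusion.** The point holds in a limited form. The primary set is randomised participants with both assessments, about 85 of 100 at the planned dropout, and calling it intention-to-treat sits badly with the protocol's own statement about missing outcomes. The restriction is unnecessary for the model named. Its cost is a bias of about 0.02 to 0.04 SD against a planned 0.4 SD, arising only if dropout depends on the pretest differently in the two arms. The cost in power is 0.3 percentage points, and neither the 90% statement nor the sample size needs to change. These figures assume ρ = 0.85, equal variances at the two visits and the dropout models shown. Keeping the pretests gives no protection when dropout depends on the posttest that was not seen.

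**What to change.** Two sections must change together.

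1. **Primary outcome:** compute the composite separately at each visit, requiring at least five ability scores at that visit, and delete the restriction to people with both assessments. Without this change a pretest-only participant still has no outcome to enter.
2. **Statistical analysis:** fit the group × time mixed model by REML to all randomised participants with a pretest, and report the completers' analysis as supportive.

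If the restriction is kept, name the set *randomised participants with pretest and posttest* and drop the intention-to-treat label.

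A reference-based sensitivity analysis, in which missing jigsaw-arm posttests take the counseling arm's change, is an optional and separate addition. It addresses dropout related to the unseen posttest, which the main change does not.

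The cost is wording and one refitted model, with no new data. One side effect to settle in the wording is that, with a per-visit rule, a participant's two composites may average different abilities.

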#### Participants’ expectations

To account for potential effects of participants’ expectations regarding cognitive benefits of the interventions, we will assess these expectations within the last telephone call between week 3 and 4 after the start of the intervention (t_5_, see Figs. 1 and 2). Participants will be asked (1) whether they expect that their performance in the visuospatial cognitive tests has been influenced positively since the pretest (answers: “yes” or “no”), and (2) how much they expect their performance in the visuospatial cognitive tests to change from pretest to posttest assessment on a 5-point rating scale (answers range from “improve markedly” to “decline markedly”). We will use the same questions with respect to participants’ expectations of improvement in jigsaw puzzle performance.

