Blinding of participants is by nature not feasible in behavioral intervention studies as participants are always aware of what they are doing. Thus, expectation effects can never be fully excluded. Multiple approaches to minimize expectation effects will be used and participants’ expectations with regard to performance improvement will be measured in a telephone-based interview approximately 9 days prior to the posttest assessment. Thus, it will be possible to statistically account for potential expectation effects.

Even if not expected, the selected outcomes of the study may not cover the cognitive abilities that are actually engaged and improved through jigsaw puzzling (e.g., verbal working memory) or may include abilities that are not recruited and improved through the intervention (e.g., cognitive flexibility). To prevent this problem, the selection of the outcomes was based on a cognitive task analysis of jigsaw puzzling that indicated the expected cognitive demands [58, 59]. Furthermore, we will assess the association between the outcome measures and jigsaw puzzle skill at baseline, in order to validate the recruited cognitive abilities of jigsaw puzzling [60] and the transfer potential of gains in jigsaw puzzle performance on gains in the respective outcomes [61]. Finally, there is a not fully preventable risk that gains in outcomes may be a result of skill acquisition or newly learned strategies rather than the improvement of broad cognitive abilities [14]. However, in contrast to many previous cognitive training studies, we use a large set of transfer tasks and these task paradigms are substantially dissimilar from the training task. Thus, we avoid the risk that skill-induced or strategy-induced gains in single and structurally similar tasks with the training task will be misinterpreted as gains in broad cognitive abilities.

Finally, we cannot fully exclude that the cognitive health counseling intervention that is conducted in both groups may have a differential effect between the groups. However, we will assess this potential by evaluating group differences in behavioral changes in cognitive, physical, and social activities, and in Mediterranean diet. In additional analyses of the group effect on the study outcomes, we will statistically account for these behavioral changes (see “Statistical analysis”).

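### The additional analyses adjust for four variables measured after unblinded allocation as if they were confounders, so the adjusted group coefficient is not the effect of assignment

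*Protocol article*

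**What the plan says.** The Statistical analysis section of the protocol article makes the group × time interaction the primary test, by intention to treat, and names no covariates for it. It then adds: "In additional analyses, we will account for potential confounding variables such as baseline performance". The list that follows mixes variables fixed before allocation (baseline performance, age, education) with others that are not: "the pretest-posttest change in these activities, Mediterranean diet in the past 4 weeks, and pre-posttest change in diet, age, education", and "participants’ test motivation at the posttest assessment, and their expectations of cognitive benefits".

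The timing is explicit elsewhere in the article:

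- **Allocation** is disclosed at t2D, straight after the pretest and the face-to-face counselling (Procedure). Participants cannot be blinded.
- **Expectations** are asked "within the last telephone call between week 3 and 4 after the start of the intervention" (Participants’ expectations).
- **Motivation:** "One item on a 5-point rating scale at the posttest assessment (t_6_) will assess test motivation" (Blinding section).
- **Change in activities and in diet** needs the posttest value by definition.

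The Discussion offers adjustment as the answer to two acknowledged limitations. On expectations: "Thus, it will be possible to statistically account for potential expectation effects". On differing responses to counselling: "we will statistically account for these behavioral changes".

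**The concern.** Confounding of the group comparison would need a common cause of allocation and outcome, and randomisation rules that out. A variable measured after allocation is either unaffected by it, so that adjustment is not needed to remove bias, or affected by it. If it is affected, conditioning on it changes what is estimated.

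The protocol itself gives reason to expect a shift. On expectations, the Blinding section says: "As differential expectations between groups are still likely to some degree and cannot be completely excluded". The Discussion allows that counselling may change behaviour differently in the two groups. Thirty hours of puzzling could also displace other leisure activities or add to them.

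The expectation item has a further difficulty. Its first question asks whether participants think their test performance has already been influenced for the better since the pretest. After three to four weeks of puzzling, the answer may partly reflect a real gain, and adjusting for it would then remove part of the effect under study.

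What is at stake is the reading of the adjusted results. A coefficient that shrinks, grows or appears because of conditioning could be taken as the puzzle effect with expectations and counselling removed.

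**Working it through.** **1. The plan's own figure.** Inputs from Power analysis: 50 per group, 15% dropout, f = 0.1, r = .85, α = 0.05. Completers: 100 × 0.85 = 85, or about 42 per arm. For a 2 × 2 within-between interaction:

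- λ = N × 2 × f² / (1 − r) = 85 × 2 × 0.01 / 0.15 = 11.33, on 1 and 83 degrees of freedom. Power is 91.4%.
- With N = 84, λ = 11.20 and power is 91.1%.

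The stated 90% is reproduced to within two points. It refers to the primary test, which does not contain the covariates at issue.

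**2. Scale.** f = 0.1 corresponds to a difference in change of 4f = 0.40 baseline SD. With equal pretest and posttest SDs, Var(change) = 2(1 − .85) = 0.30, so the SD of change is √0.30 = 0.548 baseline SD.

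**3. Covariate on the causal path (mediator).** Let allocation shift the covariate by *a* (in its own SD), and let the covariate carry *b* baseline SD of change per SD. With a total effect of 0.40 and no other bias, the adjusted coefficient is 0.40 − a·b. The values of *a* and *b* are assumptions, because the article gives none.

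| a | b | Adjusted coefficient |
|---|---|---|
| 0 | any | 0.40 |
| 0.5 | 0.10 | 0.40 − 0.05 = 0.35 |
| 0.5 | 0.20 | 0.40 − 0.10 = 0.30 |
| 1.0 | 0.10 | 0.40 − 0.10 = 0.30 |
| 1.0 | 0.20 | 0.40 − 0.20 = 0.20 |
| −0.5 | 0.10 | 0.40 + 0.05 = 0.45 |
| −1.0 | 0.20 | 0.40 + 0.20 = 0.60 |

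The last two rows describe a beneficial behaviour that rises more in the counselling-only arm. Adjustment then moves the estimate upward.

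**4. Covariate sharing an unmeasured cause with the outcome (collider), true effect zero.** If the covariate has no effect on the outcome but correlates *c* with change within arms, the adjusted coefficient is −a·c·√0.30:

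- a = 0.5, c = 0.2: 0.5 × 0.2 × 0.548 = 0.05 in size.
- a = 1.0, c = 0.4: 1.0 × 0.4 × 0.548 = 0.22 in size.

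The sign is negative when *a* and *c* have the same sign and positive when they differ.

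**5. Simulation check.** A separate set of assumed values was simulated with N = 85 and 4,000 replicates. Here slopes are per SD of change, so the expected mediator coefficient is 0.40 − a × slope × 0.548.

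- Mediator, shift 0.3 and slope 0.2: 0.367 (formula 0.367).
- Mediator, shift 0.5 and slope 0.3: 0.315 (formula 0.318).
- Mediator, shift 0.8 and slope 0.4: 0.225 (formula 0.225).
- Shared cause under the null, shift 0.5 and loadings 0.4 (c = 0.16): −0.045, with 6.5% rejections at the 5% level.
- Shared cause under the null, shift 0.8 and loadings 0.5 (c = 0.25): −0.108, with 13% rejections.
- No shift, true effect 0.40: 0.40.

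The unadjusted estimate stayed at the true value in every scenario.

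**The case against.** The strongest reply is that the trial's main result does not depend on these models. The covariates belong to additional analyses only, and the primary test and its power are untouched. That stands in full.

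The aim is also legitimate. In a behavioural trial that cannot blind participants, it is reasonable to ask whether a group difference persists given expectations or concurrent behaviour change. That is a direct-effect question, and the article takes it seriously. It uses three design measures to equalise expectations and motivation, explains why expectations are asked before the posttest visit, concedes that expectation effects cannot be fully excluded, and plans to compare behaviour change between groups. All of this stands. It does not rescue the label, because a direct effect needs the assumption of no unmeasured mediator-outcome confounding. The article does not state that assumption and presents the analysis as confounder adjustment.

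The sizes shown rest wholly on assumed inputs. That also stands, and they are only an illustration.

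A reader might infer that the adjusted models will decide whether the puzzle effect is believed, or that they serve as its robustness check. The article gives them neither role. Where it speaks of robustness, it means the per-protocol analysis.

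**Conclusion.** The point holds, for the additional analyses only. Four variables measured after unblinded allocation are classed as confounders, which they cannot be. If allocation shifts them, the adjusted group coefficient is neither the total effect of assignment nor, without a further assumption, a direct effect. The statements that expectation effects and behavioural changes can be statistically accounted for therefore do not follow from the planned adjustment.

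The size is unknown. Under the assumed shifts and slopes, a true effect of 0.40 baseline SD is estimated at 0.35 down to 0.20, or above 0.40 if the shift runs the other way. Under a true null, a shared unmeasured cause produces an estimate of 0.05 to 0.22 baseline SD in size. With no shift there is no bias.

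It would be tempting to conclude that adjustment must remove part of the puzzle effect, or that the primary result is at risk. The documents support neither. The direction is open, and the primary analysis and its stated 90% power are unaffected. This is a moderate fault of specification and interpretation that should be corrected.

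**What to change.** 1. Limit confounder-type adjustment to variables measured before allocation: baseline composite, age, MMSE, education, pretest activity count and pretest diet. State that the activity count and diet are the pretest values, since the covariate list does not give their time point.
2. Keep the planned comparison of activity and diet change by arm, and add t5 expectations and t6 motivation to it.
3. Move any model that conditions on the four post-allocation variables to an analysis labelled exploratory mediation, and state its assumption of no unmeasured mediator-outcome confounding.
4. Qualify the two Discussion statements: such models can explore the role of expectations and behaviour change under that assumption, but cannot remove it.

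The cost is wording in the Statistical analysis and Discussion sections. No new data are needed, and the sample size and primary test stay as they are.
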